## Abstract

**Background:**

Point-of-care ultrasound (POCUS) has been used in various vascular access contexts; however, to date, it has not been widely adopted in haemodialysis clinics. People with end-stage kidney disease receiving haemodialysis require an arteriovenous fistula (AVF), arteriovenous graft (AVG), or central venous access device (CVAD) in order to access their blood for therapy/treatment. Cannulation issues, such as haematoma and extravasation, related to AVFs and AVGs are common. This pilot and feasibility study will assess the feasibility of a randomised controlled trial aimed at evaluating whether POCUS-guided cannulation results in more successful and accurate AVF needle placement than the standard practice of blind cannulation.

**Methods:**

A controlled, random order crossover design will be used to evaluate two clinical conditions: (1) POCUS-guided cannulation and (2) standard practice of blind cannulation, when used by haemodialysis nurses. The feasibility of conducting this type of trial for these two clinical conditions will be assessed through recruitment, retention, and attrition rates; perceptions of acceptability; implementation measures; and assessment of methods of data collection. Clinical outcomes to be assessed are overall cannulation success on first attempt, accuracy of needle tip placement, number of extravasations, procedural time, and patient and nurse perceptions. The setting is a 16-chair dialysis unit in regional Australia. Participants will include adult haemodialysis patients with an AVF in situ for greater than 2 months and haemodialysis-trained registered nurses working full- or part-time. Clinical outcomes will be analysed using generalised linear mixed models. Feasibility data will be reported using descriptive statistics. Qualitative audio data will be digitally recorded, transcribed verbatim, and analysed using thematic analysis.

**Discussion:**

Point-of-care ultrasound for cannulation has the potential to promote high-quality, safe nursing care and decrease cannulation damage for patients on haemodialysis. Due to the lack of evidence for patient benefit and its innovative and niche use in haemodialysis centres, POCUS is currently only specified in one international guideline. This study will inform sample size calculations for a future multi-site trial.

**Trial registration:**

Australian New Zealand Clinical Trials Registry, (21/11/2017) ACTRN12617001569392

## Background

To facilitate the removal of toxins from the blood via haemodialysis, three vascular access options are available: arteriovenous fistula (AVF), arteriovenous graft (AVG), or central venous access device (CVAD). Creation of an AVF involves surgical attachment of a vein to an artery, thus making a hybrid arterialised vein. Although the AVF allows access to the blood, maturation issues can arise from poor arterialisation or vessel calcification, particularly in older patients and in patients with peripheral vascular disease and/or diabetes [1]. Diabetes is currently the leading cause of renal failure among patients starting dialysis [2]. In 1991, approximately 12% of the patients starting on haemodialysis were diagnosed with diabetes compared to 72% in 2016 [3]. In 1987, there was only one reported case (0.2%) of a patient over the age of 75 years starting haemodialysis and only 9% had peripheral vascular disease, compared to 25% and 23%, respectively, in 2016 [3]. Thus, the proportion of patients commencing dialysis with poorer quality vessels is increasing.

An AVF is the patient’s lifeline, and the role of the nurse is to protect and maintain that lifeline with minimal adverse outcomes [4]. Cannulation complications, particularly in relation to constant-site puncture and extravasation are common, leading to poor patient outcomes [5]. An AVF may be deemed clinically ready for cannulation, but the cannulator’s skill level may have an effect on the success or failure of the cannulation process [6]. With rising numbers of patients with poor vessels, the skill level and accuracy of the cannulator are even more critical.

A recent audit of the number of miscannulations experienced by patients in one 16-chair regional satellite haemodialysis unit over a 6-month period showed that between 5 and 25 miscannulations occurred per month. Patients who endure numerous miscannulations, some leading to aborted dialysis sessions, often have a tunnelled, cuffed CVAD inserted [7] to enable dialysis treatment. Central venous access devices are inserted into the internal jugular vein and tunnelled through the superior vena cava, where the tip sits at the junction of the right atrium. Complications with CVADs include malpositioning, fibrin formation blocking the lumen, clots forming inside the lumen, exit site or tunnel infection, and endocarditis, with the latter potentially causing sepsis or death [8]. Use of CVAD in the haemodialysis population, due to their higher susceptibility to infection, is associated with more hospitalisations, higher infection rates, and an increased mortality rate compared with patients who have an AVF or AVG [9]. Given these complications, the ultimate aim of planning and implementing haemodialysis vascular access care is to avoid the use of CVAD whenever possible. Ways to avoid the need for CVAD insertion include increasing the skill level of the cannulators and using point-of-care ultrasound (POCUS) to guide needle insertion to avoid miscannulations, area puncture, and subsequent damage to the AVF or AVG.

Studies in peripheral vein cannulation have shown positive results with the user of POCUS guidance, i.e. improved cannulation accuracy and decreased adverse events. Since 2013, four systematic reviews have been published of randomised controlled trials (RCTs) to test the use of ultrasound-guided peripheral cannulation [10–13]. Conclusions drawn from the systematic reviews were mixed, with two finding evidence (based on cannulation success rates) to support the use of POCUS-guided peripheral cannulation in patients with known difficult access. However, no evidence was found supporting reductions in procedural time or the number of cannulation attempts [10, 13].

Point-of-care ultrasound is currently specified only in the Canadian Association of Nephrology Nurses and Technologists’ (CANNT) recommendations for the management of vascular access. Recommendation 4 (determination of cannulation sites) indicates: ‘The use of portable ultrasound for access assessment and ultrasound-guided cannulations can optimize cannulation and ensure correct needle placement’ ([14], p. 15). However, this claim is only supported by opinion and not by empirical evidence. Purportedly, the lack of uptake of POCUS in current practice is due to the lack of evidence regarding its efficacy in decreasing cannulation adverse events. Therefore, the purpose of this pilot and feasibility study is to assess patient outcomes associated with the use of POCUS and to generate data that will inform a future multi-site study. This study will assess the feasibility of the proposed design and processes and determine the estimated recruitment required to power a larger multi-site study to test the efficacy of the use of POCUS for haemodialysis cannulation.

## Methods/design

### Aims

The overall aims of this project are to (1) examine the feasibility of the study design and acceptability to nurses and patients of the use of POCUS for guided (dynamic) cannulation in haemodialysis patients and (2) promote successful needle insertion for patients undergoing haemodialysis. These overall aims inform specific methodological and clinical aims, respectively, (1) to assess the feasibility of the proposed design and processes and inform sample size calculations for a larger multi-site study to test the efficacy of the use of POCUS for haemodialysis cannulation and (2) to determine whether POCUS-guided needle insertion improves successful cannulation and cannulation accuracy.

For the purposes of this research, successful cannulation is defined as the needle for haemodialysis being inserted without miscannulation or manipulation. Miscannulation is defined as the needle requiring reinsertion/replacement as a result of extravasation or misalignment with the vessel lumen. All POCUS-guided insertions will be performed using dynamic real-time ultrasound guidance.

The feasibility of study design and methods for measurement of POCUS-guided cannulation versus blind cannulation will be assessed using the feasibility framework advanced by Bowen et al. [15]. The following aspects will be evaluated: recruitment, retention, and attrition of both patients and nurses; methods of data collection; acceptability by both patients and nurses; and demand, implementation, and integration (see Table 1).

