Specific data collected at each haemodialysis session in relation to the nurse cannulator, patient, and dialysis machine are outlined in Table 5. The researcher will observe every cannulation in each treatment session and record the characteristics listed in Table 5 for both the venous and the arterial cannulation. A cannulation will be defined as successful (0) if the needle for haemodialysis is inserted without miscannulation or manipulation, or unsuccessful (1) if the needle extravasates the vessel or blood cannot be accessed from the needle. The number of miscannulations in a session will then take values 0, 1, or 2. For example, a nurse cannulates with the first (arterial) needle and extravasates the vessel, the needle is removed, and pressure applied to the site. This is recorded as ‘1’. In a second attempt, the arterial needle is appropriately placed in the vessel, i.e. it is successful, so this is recorded as ‘0’. The venous needle is also inserted successfully and recorded as ‘0’. The total number of miscannulations for this patient would be ‘1’. In consultation with management of the dialysis unit, the maximum allowable number of blind cannulations for a patient treatment is set at four, a maximum of two cannulations per site. For example, if a nurse miscannulates twice on the arterial point using the standard practice of blind cannulation, they would then use POCUS guidance to cannulate the third time. This information will be recorded by the researcher observing the process. If the cannulator deems POCUS guidance necessary after one miscannulation, this is acceptable and will be documented as above.

**Table 5 Tab5:** Data collected during the study

Nurses	Patients	Dialysis machine
Sitting or standing to cannulate	Patient arm position	Pump speed (Qb)
Use of gloves (sterile or non-sterile)	Patient-reported pain score (scales 1–10) each needle	Venous and arterial line pressures
Ultrasound probe held longitudinal or transverse	Patient-reported perception of the cannulation experience (scales 1–10)	Any initial pressure alarms
Cannulate in one or two motions	Patient additional comments re-cannulation or ultrasound process	
Needle manipulation once inserted	Ultrasound images in both transverse and longitudinal planes	
Time from tourniquet application until machine started		
Miscannulations (needle removed and re-sited)		
Nurse-reported perceptions of the use of ultrasound

**Table 6 Tab6:** Feasibility assessments

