Tool	Assessing	Participants	Time period
Structured observational tool	Implementation: participation rates (number of participating patients or nurses related to number of eligible patients or nurses). Overall recruitment, retention, and questionnaire completion rates	Patients Nurses	Throughout the data collection phase
Patient satisfaction survey	Acceptability: patient satisfaction with cannulation technique, use of point-of-care ultrasound	Patients	After each cannulation
Nurse satisfaction survey	Acceptability: nurse satisfaction with cannulation technique and use of point-of-care ultrasound	Nurses	After first cannulation with ultrasound After the half way point of the cannulation data collection
Researcher study notes (diary)	Implementation: protocol adherence by nurses; issues verbalised by nurses, other staff, or patients regarding the study protocol, reasons for drop-out for both patients and nurses	Patients and nurses	Throughout data collection phase
Image assessor measurement survey	Implementation: image assessor’s confidence in accuracy of measurements	Image assessor	Following completion of all needle placement measurements
Structured interview or focus group	Acceptability, demand, implementation, and integration: suitability, usability, barriers and facilitators, sustainability	Nurses	Following completion of the cannulation data collection phase

Once haemodialysis is started, the vascular access nurse expert, using the Terason uSmart 3200 T ultrasound, will take static ultrasound images in both transverse and longitudinal planes, save the images to a portable storage device, and print them for image assessor review.

A third person (image assessor), who is experienced in renal vascular access, will review the images and record data on needle positioning. The image assessor will be blinded to patient, nurse, and condition and will measure (with a ruler) the location of the needle relative to the right and left side (transverse image only) of the vessel and the top and bottom of the vessel (transverse and longitudinal images). The image assessor will complete a short, structured survey at the end of the data collection phase to capture their perceptions about the ease of conducting measurements, the image quality, and their confidence in accuracy of their measurements (see Fig. 1).

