### Data analysis

Patients’ demographic and clinical data and nurses’ demographic and experience data will be reported as means and standard deviations or frequencies and proportions. The overall study feasibility, implementation feasibility, and acceptability will be reported using descriptive statistics. For feasibility, we will report the proportion of patients/nurses eligible for the study, the proportion of patients/nurses enrolled among those eligible, the reasons for declining participation, the proportion of patients/nurses completing the study, and the reasons for completing or not completing the study.

The implementation feasibility will be reported according to patients’ and nurses’ protocol adherence rate, the proportion of time that nurses adhered to the protocol, and the image assessor’s self-reported confidence regarding the accuracy of their measurements (Likert scale). Acceptability will be reported as the proportion of patients expressing satisfaction and the nurse satisfaction survey results related to the cannulation technique and use of point-of-care ultrasound-guided cannulation. Other data related to extravasations and nurse cannulation and ultrasound experience will be summarised using rates and proportions.

Data collected from semi-structured individual and focus groups interviews will be audio-recorded, transcribed verbatim, de-identified, and undergo content and thematic analyses based on a naturalistic inquiry approach.

The potential effect of the POCUS-guided cannulation on the clinical outcomes (miscannulations [0, 1, 2]), location of the needle in the vessel, and duration of the procedure will be estimated using generalised linear mixed models with link and distribution selected based on the type of outcome. The models will include the patient and nurse as random effects, and the condition, period (order in the sequence), and first carry-over effect as fixed effects.

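### Two failure rules conflict, and under the one that counts misalignment the trigger for a failure may differ between POCUS and blind cannulation

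*Protocol article*

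**What the plan says.** All places are in the protocol article.

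- **Aims, success:** "successful cannulation is defined as the needle for haemodialysis being inserted without miscannulation or manipulation".
- **Aims, miscannulation:** "Miscannulation is defined as the needle requiring reinsertion/replacement as a result of extravasation or misalignment with the vessel lumen".
- **Aims, POCUS condition:** "All POCUS-guided insertions will be performed using dynamic real-time ultrasound guidance". The blind condition has no such view.
- **Data collection, outcome measures, and procedures, scoring rule:** the success half repeats the Aims wording. The failure half scores a needle "unsuccessful (1) if the needle extravasates the vessel or blood cannot be accessed from the needle". Neither misalignment nor manipulation appears there.
- **Table 5:** one item is "Miscannulations (needle removed and re-sited"; a separate item is "Needle manipulation once inserted". No listed item gives the reason for either.
- **Same section, after Table 6:** "Once haemodialysis is started, the vascular access nurse expert, using the Terason uSmart 3200 T ultrasound, will take static ultrasound images". An assessor blinded to condition reads needle position from these images.
- **Data analysis:** miscannulations (0, 1 or 2), needle location and procedure duration are modelled as separate outcomes.

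**The concern.** There are two linked problems. First, the Aims section and the scoring rule do not define the same event, so the observer can code some needles in two ways or in none.

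Second, if the Aims definition governs, whether a needle requires re-siting for misalignment is judged on different information in each condition. Under POCUS the nurse watches the needle on a screen, so the intervention itself can reveal the misalignment and prompt the correction. Under blind cannulation a needle in the same position that yields blood shows no image, and it may simply be left and scored as a success. The static images taken after dialysis starts do not close this gap, because they feed the separate location outcome and not the miscannulation count.

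First-attempt success is the first-listed clinical outcome, and the miscannulation count is modelled. The study is also meant to inform the sample size of a multi-site trial, so an outcome triggered differently by condition could carry a distorted estimate forward. Random order and patient and nurse effects in the model do not correct that.

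**Working it through.** **1. The rules side by side**

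| First needle | Aims definition | Failure half of scoring rule | Table 5 |
|---|---|---|---|
| Extravasates, re-sited | Miscannulation | 1 | Re-sited |
| Yields blood, no extravasation, re-sited as misaligned | Miscannulation | Not 1 | Re-sited |
| Yields blood, manipulated, not re-sited | Not a success, not a miscannulation | Not 1 (and not 0 under the success half) | Manipulation |
| Yields blood, misaligned, left alone | Success | 0 | No entry in either item |

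Rows 2 to 4 can start from the same needle position. Which row applies depends on whether anyone notices the misalignment and acts on it, and a real-time image exists in one condition only. Row 3 affects success but not the modelled 0/1/2 count.

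**2. How rare the outcome is**

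The article gives no failure rate to reproduce. The Background reports an audit of 5 to 25 miscannulations a month, without a denominator or a stated definition. Assume it covers the 30 AVF patients named under Target sample size, with three sessions a week and two needles each:

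- 30 × 3 × 52/12 = 390 sessions a month; × 2 = 780 needles.
- 5/780 = 0.64%; 25/780 = 3.2% per needle.
- At full recruitment, 20 patients × 10 nurses = 200 sessions per condition; × 2 = 400 first-attempt needles.
- Expected failures per condition: 400 × 0.64% = 2.6, to 400 × 3.2% = 12.8.

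**3. How small an extra share would matter**

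Let p be the failure rate without detection-driven events. Let m be the extra share of needles counted as failures under POCUS, and b the extra share under blind cannulation. The article gives neither m nor b, so both are assumed. Observed rate = p + (1 − p) × extra share.

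Suppose POCUS truly halves failure and b = 0. The benefit is cancelled when m = (p/2)/(1 − p/2):

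- p = 0.64%: m = 0.32%, or 1.3 of 400 needles.
- p = 3.2%: m = 1.6%, or 6.5 of 400.
- p = 10% (assumed, to show the range): m = 5.3%, or 21 of 400.

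**4. Whether the direction is fixed**

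With p = 3.2% under blind cannulation and a true risk ratio of 0.50:

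| m (POCUS) | b (blind) | Observed risk ratio |
|---|---|---|
| 2% | 0% | 0.0357/0.0321 = 1.11 |
| 2% | 2% | 0.0357/0.0514 = 0.69 |
| 2% | 5% | 0.0357/0.0804 = 0.44 |

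The first two rows move the result against POCUS and the third moves it in favour. The sign depends on m relative to b.

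**5. Under the literal failure half of the scoring rule**

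A needle that yields blood without extravasation scores no failure in either condition. The mechanism then adds nothing to the failure code.

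**The case against.** The strongest answer is that the scoring rule is the operative one. It already rests on signs available in both conditions, and under it the mechanism disappears. That would settle the matter if the rule stood alone. But its own success half brings back miscannulation and manipulation, the Aims section defines miscannulation to include misalignment, and the Table 5 item counts any re-sited needle. The article does not say which prevails.

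A reader might infer that the comparison is definitely biased against POCUS. The document does not support that. Blind needles may also be repositioned because of poor blood return, line pressures or alarms (Table 5 records the last two). Searching without an image may add manipulation, and guidance may prevent misalignment before it occurs. Nor does the article say that nurses will re-site a needle that yields blood because it looks off-centre. A reader might also infer that manipulation inflates the modelled miscannulation count; as worded, it does not.

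Two further points have weight. An image-prompted re-siting is still a second puncture for the patient, so dropping it from the results would hide a possible cost of the intervention in one condition only. And the article states that the study will not provide outcomes on effectiveness; its primary outcomes under the methodological aim are feasibility measures. That limits the consequence, but the study is still meant to inform the later sample size.

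Finally, a condensed article may not list every field on the form, so a missing reason item would not be a finding by itself. It matters here because the stated definitions make the reason decisive.

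**Conclusion.** The point holds in a limited form. The Aims definition and the failure half of the scoring rule contradict each other and must be reconciled; that rests on the text alone. Under the Aims definition and Table 5, the misalignment component may be triggered differently by condition, plausibly but not certainly against POCUS.

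The size of any distortion is unknown. The article does not give the share of image-prompted corrections or its blind counterpart, and every rate used for them above is an assumption. What can be said is that at a base rate of 0.64% to 3.2% per needle, itself resting on the assumed audit denominator, a handful of extra events among 400 needles is enough to change the estimate materially. The change is best made before cannulations are observed, because the reason for a correction may not be recoverable afterwards.

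**What to change.** 1. Reconcile the Aims section and the scoring rule into one failure rule, applied identically in both conditions and based on signs available in both: the first needle extravasates, or blood cannot be accessed from it. Report manipulation separately, and state its place in the success definition in the same words in both sections.
2. Add one field to the observation sheet giving the reason for each re-siting or manipulation: clinical sign, or seen on ultrasound only.
3. Report two counts by condition: failures by clinical signs, and all re-sitings including those prompted by the image. No extra puncture is then hidden.
4. Compare alignment between conditions only on the post-start images read by the blinded assessor, as the separate location outcome already allows.

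The cost is one tick-box, reworded definitions and two reported counts in place of one. No extra patients, staff or procedures are needed. The remaining weakness is that the reason would be judged by an observer for whom the article states no blinding, which is why the total count should always stand beside the clinical-sign count.
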